### Overall success of the intervention

The overall success of the intervention and decision to evaluate it in a larger scale trial will be determined with both primary and secondary outcomes. A final decision about the protocol will be made upon completion of the study [32]:Stop (main study not feasible). None of the primary feasibility outcomes are met *and* a negative trend is observed in secondary outcomes *or* other adverse effects are reported.Continue but modify protocol (feasible with modifications). One or more of the primary feasibility outcome measures are not met.Continue without modifications (feasible as is). All of the primary feasibility outcomes are met *and* a positive trend is observed on both secondary outcomes (ToM and social competence).

Trends on secondary outcomes will be determined with visual analysis, as described in the “Statistical methods” section. A negative trend would be indicated by scores that fall below the baseline mean and positive trends by scores that fall above the baseline mean [60]. Scores that are comparable to baseline or fluctuate around the baseline mean would indicate neither a positive nor negative trend. A negative trend for ≥ 50% of participants would be sufficient to stop the main study (decision a). A positive trend on ≥ 50% of participants will be considered sufficient to continue the study, with or without modifications (decisions b or c). Smith [60] provides further details about this method. Participants included in the pilot study will not be included in an ongoing trial that results from this research to reduce the potential for bias in results.

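### The progression rule conflicts with itself on a negative trend, leaves some outcomes without a usable decision, and gives two decisions in others

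*Protocol article*

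**What the plan says.** All the relevant text is in the protocol article, section Overall success of the intervention. The list reads:

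- Decision a, stop: "None of the primary feasibility outcomes are met *and* a negative trend is observed in secondary outcomes *or* other adverse effects are reported".
- Decision b, continue but modify: "One or more of the primary feasibility outcome measures are not met". There is no condition on the trend.
- Decision c, continue as is: "All of the primary feasibility outcomes are met *and* a positive trend is observed on both secondary outcomes (ToM and social competence".

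The paragraph after the list defines trends against the mean of the two baselines and allows a third state: "Scores that are comparable to baseline or fluctuate around the baseline mean would indicate neither a positive nor negative trend". It then adds two threshold sentences. One is "A negative trend for ≥ 50% of participants would be sufficient to stop the main study (decision a". The other is "A positive trend on ≥ 50% of participants will be considered sufficient to continue the study, with or without modifications (decisions b or c".

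**The concern.** The choice between a, b and c is what the pilot is meant to deliver. The Abstract, Statistical methods and Conclusion all say that the results will decide whether a larger trial follows. A progression rule fixed in advance is useful only if each result leads to one decision. Here the list and the threshold sentences can send the same result to different decisions, and some results reach none. The choice would then be made after the data are seen, in an open-label study where trends are judged by eye.

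The undecided region includes foreseeable results. The Background says that training has been broadly effective for Theory of Mind (ToM), while gains in social competence appeared in some studies and not in others. A feasible programme with ToM improved and social competence flat is therefore plausible.

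**Working it through.** The document gives no figure to reproduce, so the check is one of logic. Cross feasibility (none, some or all met) with the ToM trend (+, 0, −) and the social competence trend (+, 0, −). With no adverse effects this gives 3 × 3 × 3 = 27 combinations.

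**Side by side, no adverse effects**

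| Feasibility | Trends | List | Threshold sentences |
|---|---|---|---|
| None met | negative | a and b | stop (a) |
| Some met | negative | b | stop (a) |
| All met | negative | no decision | stop (a) |
| All met | both neutral | no decision | no decision |
| All met | one positive, one neutral | no decision | continue (b or c) |
| All met | both positive | c | continue (b or c) |

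**1. Conflict.** The text does not say whether a trend is negative when either outcome is negative or only when both are. Of the 9 trend pairs, 5 have at least one negative and 1 has both negative. The list fails to give a in the rows for some met and all met. The list and the stop sentence therefore disagree in 2 × 5 = 10 of 27 combinations on the first reading and in 2 × 1 = 2 of 27 on the second. The conflict remains whichever way the *and … or* in decision a is grouped.

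**2. Gap.** With all feasibility outcomes met, b fails because nothing is unmet, and c holds only for (+,+). The list alone therefore leaves 9 − 1 = 8 trend pairs without a decision. The stop sentence settles 5 of these (either outcome negative) or 1 (both negative), which leaves 3 or 7. Two kinds fail on every reading tried:

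- (0,0): no sentence applies.
- (+,0) and (0,+): the paragraph allows b or c, but b needs an unmet feasibility outcome and c needs "a positive trend is observed on both secondary outcomes (ToM and social competence".

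**3. Overlap.** The condition "None of the primary feasibility outcomes are met" implies the condition for b, so total feasibility failure with a negative trend satisfies both a and b. At n = 10 a 5/5 split, and at n = 12 a 6/6 split, is 50% negative and 50% positive, so it meets both thresholds. If adverse effects alone trigger a, then adverse effects with some outcomes met satisfy a and b. With all met and both trends positive, they satisfy a and c.

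**4. Illustration of the gap's size.** Visual analysis sets no numeric rule, so these are assumptions, not figures from the plan: independent equal-variance scores at two baselines and two later visits, no effect, independent outcomes, a child positive if both later scores exceed the baseline mean and negative if both fall below it, and the 50% applied per outcome.

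- The two differences from the baseline mean have correlation 0.5/1.5 = 1/3. P(positive) = P(negative) = 1/4 + asin(1/3)/(2π) = 0.304, and P(neutral) = 1 − 2 × 0.304 = 0.392.
- P(at least 50% positive on one outcome) = P(X ≥ 5 of 10) = 0.157, or P(X ≥ 6 of 12) = 0.124. The same values hold for negative.
- P(exact tie) = 0.0017 (n = 10) or 0.0006 (n = 12).
- P(no threshold reached on one outcome) = 1 − 2 × 0.1574 + 0.0017 = 0.687, or 1 − 2 × 0.1244 + 0.0006 = 0.752.
- P(no threshold reached on either outcome) = 0.687² = 0.47 (n = 10), or 0.752² = 0.57 (n = 12).

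If all feasibility outcomes are also met and no adverse effects are reported, such a pilot has no decision under either the list or the threshold sentences.

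**The case against.** The strongest reply is that the two 50% sentences are definitions. They follow the definition of a trend and refer back to decisions a, b and c, so they may only say how many children make a group trend. The sentence on positive trends supports this, because feasibility, not the trend, must choose between b and c. On this reading the conflict disappears. However, the text calls a negative trend sufficient to stop and does not say that it only defines a term. The definitional reading also removes the stop sentence as a separate rule, so all 8 of the 9 trend pairs with full feasibility become undecided. It trades the conflict for a wider gap.

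A second reply is that the Social competence subsection says contradictory findings on different measures will be used to revise methods and select outcome measures for an ongoing trial. That concerns disagreement between measures. It does not assign a stop or continue decision.

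Two stronger readings should not be drawn:

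- A reader might infer that the plan gives no decision whenever all feasibility outcomes are met and the trends are not both positive. The threshold sentences do give stop or continue in several of those cases.
- A reader might infer that almost every fully feasible pilot would be undecided. Under the same no-effect assumptions, positive trends on both outcomes occur in 0.157² = 2.5% (n = 10) or 0.124² = 1.5% (n = 12) of pilots, so the list alone leaves about 98% undecided. That figure ignores the threshold sentences and applies only if every feasibility outcome is met. Any miss gives b by the list, and the documents do not allow an estimate of how often all are met.

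**Conclusion.** The point holds. The rule conflicts with itself on the literal reading, leaves at least (0,0), (+,0) and (0,+) without a usable decision when feasibility is fully met, and gives two decisions in other cases. These conclusions rest on the wording alone. The extent of the conflict, 2 or 10 of 27 combinations without adverse effects, depends on whether one or both outcomes must be negative, which the text does not settle.

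The 47% and 57% are illustrative. They assume no effect, independent scores and outcomes, and two post-baseline scores, although the primary social competence measure is completed weekly. They bear on the gap only if all feasibility outcomes are met, and they take trends as unrelated to feasibility.

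This is a should-fix. The framework is exploratory and no test or error rate depends on the rule, but it governs the pilot's main decision.

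**What to change.** Before data are seen, replace the list and the threshold sentences with one table: feasibility (all, some or none met) by trend (positive on both, mixed or neutral, negative), with exactly one decision in each cell. The investigators choose the decisions. The text should also:

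- state one negative-trend rule and apply it in every feasibility row;
- say whether the 50% applies to each outcome separately, and whether a negative result on one outcome is enough;
- say how an even positive/negative split is resolved;
- state explicitly how reported adverse effects enter the decision, in place of the ambiguous *and … or*.

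The cost is rewording one section. No extra participants, assessments or analyses are needed.

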Theory of Mind (ToM) refers to the ability to understand the thoughts, intentions, beliefs and emotions of others and oneself [10]. ToM is comprised of component skills including the capacity to understand mental states, including beliefs and knowledge (cognitive ToM), and to identify and communicate emotions (affective ToM) [10]. Interventions targeting ToM have been developed and trialled for children with other neurodevelopmental conditions, including autism spectrum disorder (ASD) and hearing impairment [11–13]. For these groups, ToM interventions have been broadly effective at improving ToM [14, 15], with a recent meta-analysis finding medium-size improvements in children’s ToM following training (Hedges’ *g* = 0.747) [14]. Improvements in everyday social competence following ToM training have been documented in some studies [16, 17] but not others [11, 12]. The efficacy of prior interventions was found to depend on whether the components included in training were appropriate for age and ability level of the target group [14]. This included the suitability of ToM modules (i.e. targeting cognitive and/or affective ToM) and whether strategies were included to assist with the acquisition and/or generalisation of ToM skills (i.e. language exercises, executive functioning [EF] strategies and cognitive behavioural therapy [CBT] skills).

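### The stop and continue counts share one inclusive 50% cutoff, name no outcome and set no precedence, so a mixed result can meet both

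*Protocol article*

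**What the plan says.** The section Overall success of the intervention first gives a three-way list.

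- Decision a, stop: "None of the primary feasibility outcomes are met *and* a negative trend is observed in secondary outcomes *or* other adverse effects are reported".
- Decision b, continue with modifications: "One or more of the primary feasibility outcome measures are not met". It has no trend condition.
- Decision c, continue as is: all feasibility outcomes are met and "a positive trend is observed on both secondary outcomes (ToM and social competence".

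It then defines a trend for the individual child: "A negative trend would be indicated by scores that fall below the baseline mean and positive trends by scores that fall above the baseline mean". It also allows a neutral class: "Scores that are comparable to baseline or fluctuate around the baseline mean would indicate neither a positive nor negative trend".

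Two counting sentences follow. For stopping: "A negative trend for ≥ 50% of participants would be sufficient to stop the main study (decision a". For continuing: "A positive trend on ≥ 50% of participants will be considered sufficient to continue the study, with or without modifications (decisions b or c". Neither names an outcome, and no tie rule or order of precedence is given. The planned sample is 10 to 12 children (Participants and sample size), and there are two secondary outcomes, ToM and social competence (Objectives).

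**The concern.** Two conditions that lead to opposite decisions should not both be satisfiable by the same data unless the plan says which prevails. Here both cutoffs include exactly 50%, both are called sufficient, and there are two outcomes to which each might apply. The outcomes need not move together. The Background notes that "Improvements in everyday social competence following ToM training have been documented in some studies [16, 17] but not others [11, 12".

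The rule decides whether a larger trial goes ahead. Trends are judged visually in an open-label study, so an unresolved conflict leaves the decision to be chosen once the results are known.

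**Working it through.** The plan derives no figure for these cutoffs, so there is none to reproduce. The check is logical first, with illustrative probabilities after it.

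**1. Across outcomes, literal reading.** Take n = 10, with 6 children positive on ToM and 6 negative on social competence. The continue count is met on ToM (6/10 ≥ 50%) and the stop count on social competence (6/10 ≥ 50%). Nothing here depends on n being even or on there being no neutral children. The same conflict can arise at n = 11 or 12.

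**2. Within one outcome.** Both counts hold only if positives ≥ n/2 and negatives ≥ n/2. Since positives + negatives ≤ n, both must equal n/2 and no child can be neutral. Listing all splits for n = 8 to 12 gives 4/4, 5/5 and 6/6 at n = 8, 10 and 12, and none at n = 9 or 11.

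**3. Counts read as defining the trend element of the list.** Decision a (trend arm) needs no feasibility outcome met, and decision c needs all met, so a and c cannot coincide by this route. Decision b needs at least one feasibility outcome not met, which is automatically true when none is met. So whenever a is reached through the trend arm, b's stated condition holds too. If the positive count is also met, the continue sentence supports b while the stop sentence supports a.

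**4. Illustrative size.** These assumptions are mine, not the plan's:
- each child's four scores on an outcome vary independently around that child's level, with SD 1 (within-child, occasion-to-occasion);
- a child is positive if both later scores exceed the mean of the two baselines, negative if both fall below it, and otherwise neutral;
- there is one measure per outcome, and ToM and social competence are independent.

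The difference between a later score and the baseline mean has variance 1 + 1/2 = 1.5. The two differences share the baseline variance 0.5, so their correlation is 0.5/1.5 = 1/3.

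*No true change.* P(positive) = P(negative) = 1/4 + arcsin(1/3)/(2π) = 0.304, and P(neutral) = 1 − 2 × 0.304 = 0.392.

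*Exact tie on one outcome, no true change:*
- n = 10: C(10,5) × 0.304^10 = 252 × 0.304^10 ≈ 0.0017, or 0.17%
- n = 12: C(12,6) × 0.304^12 = 924 × 0.304^12 ≈ 0.0006, or 0.06%
- n = 11: impossible

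*Cross-outcome conflict, ToM gain of 0.75 SD, social competence unchanged.* Per child, P(ToM positive) is the bivariate normal probability with both limits 0.75/√1.5 = 0.612 and correlation 1/3, which is 0.572. P(social competence negative) = 0.304. Binomial tails at the inclusive cutoff give:

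| n | Count needed | P(ToM ≥ 50% positive) | P(social competence ≥ 50% negative) | Product |
|---|---|---|---|---|
| 10 | 5 | 0.783 | 0.157 | 0.123 |
| 11 | 6 | 0.688 | 0.083 | 0.057 |
| 12 | 6 | 0.787 | 0.124 | 0.098 |

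**5. Strict majority.** With > 50% required for each class, no split of n = 8 to 12 is both positive and negative on one outcome. The conflict between outcomes in step 1 remains (6 of 10 exceeds 50% on each), so a strict majority alone is not enough.

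**The case against.** The strongest reply is that the counting sentences should not be read apart from the list. The section opens by saying that primary and secondary outcomes together determine the decision, and decision c explicitly requires a positive trend on both outcomes. On that reading a child group positive on ToM and negative on social competence does not qualify for c, and a further requires every feasibility outcome to fail.

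Much of this stands. A reader might infer that the rule routinely returns stop and continue-as-is from the same data. The list does not support that through its trend conditions. What survives is the overlap of a and b when no feasibility outcome is met, and the mismatch in wording: the counts call a trend sufficient where the list makes it one of several conditions. One could take a, the more specific condition, to override b, but the article does not say so.

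Two other strong readings also fail. A reader might treat an even split on one outcome as a common event. That needs every child to be positive or negative, whereas the plan defines a neutral class, and 11 children, which is within the planned range, cannot tie. A reader might also infer from the Background that social competence is likely to fall while ToM rises. The cited evidence is of no improvement in some studies, not of decline. The Background also says that ToM impairments relate to social competence; a positive correlation between changes in the two outcomes would make opposite results less frequent than independence implies.

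Finally, the study is exploratory and no child's care depends on this rule. That limits the weight of the point but does not settle which decision the stated rule gives.

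**Conclusion.** The point holds in a limited form. Taken literally, the two counting sentences can both be satisfied at any n when the outcomes point in opposite directions; a tie within one outcome is possible but rare. Taken as inputs to the list, they leave a and b overlapping whenever no feasibility outcome is met. These conclusions follow from the wording alone.

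The cross-outcome frequency of about 6% to 12% is illustrative only and applies to the literal reading. It rests on the assumed ToM gain, unchanged social competence, independent outcomes, a single measure per outcome and the both-later-scores definition of a trend. It is not conditioned on the feasibility results. The wording should be corrected before results are seen, because the rule governs progression to a larger trial.

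**What to change.** Reword the two counting sentences to do three things.

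1. Apply the count to ToM and social competence separately with a strict majority: more than 50% of participants positive makes the outcome positive, more than 50% negative makes it negative, and anything else is neutral.
2. Say that these classes supply the trend conditions in the list, together with feasibility, and are not sufficient by themselves.
3. State in advance which decision follows when the two outcomes disagree, and which prevails when a and b both apply. That choice is for the investigators.

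The cost is a few sentences and one extra child for a positive class at even n: 6 instead of 5 of 10, or 7 instead of 6 of 12, with no change at 11 (6 in either case). This is less favourable to continuing. In the illustration above, the chance that ToM is classed positive falls from 0.783 to P(at least 6 of 10 at 0.572) = 0.561, and from 0.787 to P(at least 7 of 12) = 0.588. If that is unwelcome, keeping the inclusive cutoff and declaring an exact half/half split neutral also makes the classes exclusive within an outcome. Items 2 and 3 are needed either way.

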### Monitoring and harms

A formal data monitoring committee (DMC) was not considered necessary for the current study given its short duration and minimal anticipated risks to participants [30]. Similarly, an auditing procedure is not in place nor was this required by the governing HREC given the short duration of the intervention, single-centre administration and minimal number of anticipated recruits. A formal DMC and auditing procedure will be established if the research progresses to a larger scale trial. Children’s progress will be monitored during the study by investigators running the intervention to ensure safety and reduce risk of harm. There are no significant foreseeable risks to children participating in this study; all tasks included in the intervention and assessments are safe and similar to activities that are routinely used in child therapy and neuropsychological assessments. Nevertheless, if children experience distress or wish to stop participating at any point, investigators will deal with this appropriately. Adverse events will be immediately reported to the governing HREC and dealt with appropriately at the time they are reported. Investigators will arrange for appropriate psychological support, which may include external referral if deemed appropriate by the governing HREC.

### Consent and confidentiality

Informed consent will be obtained from all participants prior to the first assessment by study investigators. Parents/guardians and children will be provided with written PICFs that explain the study in clear, age appropriate language (see Additional file 3 for PICFs that will be used for the study). Written consent will be obtained from parents/legal guardians. Children who are deemed by investigators to have the requisite capacity and maturity to understand the research will also be asked to provide written consent by countersigning the parent/guardian consent form. As per the child consent guidelines developed by the Australian Paediatric Research Ethics & Governance Network (APREG) [62], children who are not considered to have the required capacity/maturity to consent will not sign the consent form and the signature of their parent/guardian will be considered sufficient, provided the child has been involved in the discussion and their decision to participate or not has been respected, which is also consistent with the policy of the governing HREC. Participant confidentiality will be maintained by collecting and storing de-identified data and disseminating findings in a way that ensures participants are not individually identifiable in any reports, articles, presentations or other outcomes arising from the research.

### Ancillary and post-trial care

Following completion of the study, parents/guardians will be provided with individualised feedback about their child’s participation and recommendations for post-trial care if deemed appropriate/necessary (e.g. ongoing group or individual therapy). We do not anticipate any significant harms resulting from participation in the intervention nor believe that there will be any need for compensation for loss or damages.

### Dissemination of findings

Findings will be communicated to parent/guardians in brief written reports and with parental consent, reports will also be sent to relevant healthcare professionals (e.g. neurologists, general practitioners [GPs]) involved in the child’s care. Findings will be disseminated in peer-reviewed publications and conference presentations, as well as forums run through The University of Sydney and the Australian Research Council Centre of Excellence for Cognition and its Disorders, with whom the project is affiliated. Investigators involved in designing/implementing the intervention or those who make significant contributions to the final write up of results will be eligible for authorship. Professional writers will not be used.

